**The Pathological Development of MASLD**

The pathogenesis of MASLD has been linked to the presence of one or more of the following factors: impaired lipid metabolism, insulin resistance, increased gut permeability, high-starch carbohydrates and high-fat diets, genetic factors, alteration in the inflammatory signalling and immune system pathways, endoplasmic reticulum stress and oxidative stress. All these factors play important role in the progression of MASLD to more severe stages of liver disease [10, 11].

*Gut permeability and MASLD*

The liver receives blood through both arterial and venous systems, with most of its blood flow coming from the intestines via the portal vein. This connection exposes the liver to potentially harmful substances from the gut, including translocated bacteria, lipopolysaccharides (LPS) and secreted cytokines. A primary function of the liver is to remove these substances from the bloodstream. Gut permeability is defined as weakened intestinal barrier. There are several proteins that are responsible for sealing the junctions between intestinal endothelial cells, playing a critical role in preventing harmful compounds from passing into the portal circulation. However, dysbiosis (disruption of the normal gut microbiota) can disrupt these tight junctions, leading to increased intestinal permeability and exposing both the gut lining and liver to inflammatory bacterial byproducts [12].

Growing research suggests that there is a link between gut health and the development of various liver conditions, such as MASLD and MASH. This was based on findings which indicated that individuals with MASLD exhibit higher intestinal permeability, endotoxemia (increased of plasma level of LPS) and increased bacterial overgrowth in the small intestine compared to those without the condition [13]. Additionally, liver disease has been linked to alterations in gut bacterial composition, and modifying the gut flora has been shown to influence liver damage [6].

The gut microbiota provides additional energy for the body by breaking down polysaccharides into short-chain fatty acids (SCFAs) such as acetic, propionic and butyric acid through Bacteroides. SCFAs serve as energy sources for the liver, where they play key roles in hepatic lipogenesis (fat production) and gluconeogenesis (the generation of glucose), respectively. Acetate, in particular, can be utilized as a precursor for cholesterol or fatty acid synthesis. SCFAs contribute approximately 30% of the liver's energy needs. The types and concentrations of SCFAs produced in the gut are affected by carbohydrate intake and dysbiosis, therefore alteration in gut microbiota can affect SCFAs and by that affect liver lipogenesis and gluconeogenesis [12]. Moreover, SCFAs interact with receptors such as G-protein-coupled receptors (e.g., GPR41 and GPR43) found on immune cells, influencing immune and inflammatory responses. By signalling through these receptors, SCFAs may either exacerbate or reduce inflammatory pathways, depending on their concentrations and balance within the gut lining. Butyrate, for example, may help reduce inflammation by influencing regulatory T cells in the gut lining. A human study found that faecal transplants from lean donors to patients with obesity led to significant metabolic improvements, which were associated with a notable increase in the abundance of Roseburia intestinalis, a key butyrate-producing bacterium. The overall impact of SCFAs on intestinal inflammation and permeability likely depends on the specific balance of SCFAs generated in the gut [12, 14].

Certain gut bacteria have been linked to the development of MASLD; for example, studies on obese mice have shown a 50% reduction in Bacteroides and an increase in Firmicutes compared to lean mice. Furthermore, germ-free mice exhibit a significant rise in body fat when colonized with microbiota from obese donors. On the other hand, a newly identified bacterium, Akkermansia muciniphila, is associated with a leaner body type in both humans and animal studies; high-fat diet mice treated with Akkermansia show less inflammation in fat tissue and improved glucose tolerance. The gut flora also produces enzymes that break down dietary choline—a component crucial for cell membrane integrity and lipid transport in the liver—into methylamines, which are harmful compounds linked to inflammation and liver damage. Dysregulated microbiota may lead to triglyceride buildup and exacerbate MASLD by decreasing choline availability and increasing methylamine levels [6].

There are several genes affecting the building of the epithelial barrier and the luminal microbiota and therefore their variants might increase gut permeability. One of these genes is MUC2. MUC2 is responsible for producing mucin, a key component of the mucus layer that protects the gut lining. MUC2 directly contributes to forming a physical barrier that prevents bacteria and toxins from reaching the epithelial cells of the gut. A study that was done on MUC2 knockout mice proved that absence of MUC2 increased gut permeability. Therefore, downregulation or mutation of MUC2 can increase gut permeability by reducing mucin levels [15, 16].

Gut permeability is widely measured through tracking the urinary excretion of certain sugars or sugar alcohols (e.g., lactulose, mannitol, rhamnose, sucralose), which are absorbed in the gut but minimally metabolised. The lactulose-to-mannitol excretion ratio (LMR) is the most widely used and validated marker of permeability and has even been adopted as an endpoint in clinical trials. Recent research, that has been conducted at the University of Nottingham, has validated MR measures of small bowel wall T2* as a non-invasive novel technique to investigate gut permeability in healthy volunteer [17].

**Non-invasive tests for diagnosing MASLD**

Based on National Institute for Health and Care Excellence (NICE) guidelines, liver biopsy is still the gold standard to diagnose patients with MASLD, however, it is not feasible to use it to screen all people with risk factors (central obesity (excessive abdominal fat), insulin resistance or type 2 diabetes, hypertension, and dyslipidaemia) because it is invasive, has risk of complications, and is expensive. Other non-invasive diagnostic tools include clinical, biochemical and radiographic tests such as Fibroscan™ controlled attenuation parameter (CAP). MRI can also be used to determine liver fat content [18, 19].

**Project Rationale**

Pectin is a complex soluble heteropolysaccharides that is found in the primary cell walls of higher plants and commonly used as a food additive. Pectin is classified based on the esterification degree to either high-methoxy (HM) pectin where the esterification degree is higher than 50% or Low-methoxy (LM) pectin where the esterification degree is lower than 50%. HM pectin is usually difficult to be digested or absorbed by human bodies. In contrast, LM pectin is reported to modify the gut microbiome and its metabolites, and on systematic inflammation pathway by reducing pro-inflammatory cytokines [20, 21].

*Research question*

How does dietary Low-methoxy (LM) pectin supplementation affect systematic inflammation pathways such as those mediated by gut microbiota composition and what are the impacts on general metabolic indicators in individuals with MASLD?

*Hypothesis*

LM pectin could potentially modulate gut microbiota and improve gut permeability; and could interact with Toll-like receptors (TLRs) and inhibit of their activity [15, 16]. These mechanisms are explained below.

1. Pectin effects on gut microbiota and gut permeability

- Short-Chain Fatty Acids (SCFAs) production

Pectin fermentation by gut bacteria produces a wide range of metabolites including SCFAs such as propionate and butyrate. SCFAs can play important role in lipid and glucose homeostasis by entering the peripheral circulation through portal vein and then acting on the liver and peripheral tissues. Moreover, inside the intestine, short-chain fatty acids can enhance the secretion of peptide YY (PYY) and Glucagon-like peptide 1 (GLP-1) by enteroendocrine cells and both peptides are responsible for slowing down the intestinal transit and supressing food intake. Both in vivo and in vitro studies have showed that pectin can increase SCFAs. Moreover, research has indicated that pectin can strengthen gut barrier function and reduce permeability by increasing the amount of SCFAs that can promote the production of mucus in the intestines of rodents and improve the building of tight junction. Studies showed that LM pectin produced higher amount of SCFAs compared to HM pectin [22-24].

- Modulate microbiota

The effect of pectin on gut microbiota has been studied widely through in vivo and in vitro models. Studies have shown that this effect is variable depending on the degree of esterification, chemical structure and the molecular weight of pectin. Prior studies involving rats, pigs, and humans, indicated that pectin can stimulate the growth of beneficial bacteria such as Bacteroidetes and Firmicutes. Studies reported a reduction in Bacteroidetes within the gut of MASLD patients [22, 25].

- Strengthening tight junctions

LM pectin helps reinforce the structure and function of tight junctions (protein complexes connecting epithelial cells in the gut lining). Tight junctions regulate the selective permeability of the gut, allowing nutrients and water to pass while blocking harmful substances. Studies suggest that LM pectin increases the expression of proteins involved in tight junction integrity, such as occludin. This reinforcement reduces the likelihood of molecules leaking through the intestinal barrier [26].

1. The anti-inflammatory effects of pectin

- Binds directly to Toll-Like Receptors (TLRs) and inhabits their inflammatory activity

Research using human and animal models has demonstrated that pectin has a potential anti-inflammatory effect through interacting with Toll-Like Receptors (TLRs). TLRs play crucial role in the progression of liver inflammation and steatosis. TLR2 and TLR4 are the most common TLRs associated with metabolic inflammation. TLR2 up-regulation was reported in many NAFLD animal models as well as led to development of NASH in in the liver of E3 rats. In addition, anti-TLR2 antibody reduces hepatic injury, inflammation, fibrosis and steatosis in rats with obesity-related metabolic disorder via regulation of MAPK and NF-κB pathways. Using pectin, as a promising TLR2 inhibitor [27, 28].

Pectin can directly bind to TLRs and inhibit their activity based on its degree of esterification; the higher the degree of methyl-esterification, the lower the binding to TLRs. LM pectin was able to strongly inhibit TLR2-1 induced IL-6 secretion in human macrophages [29]. In in vitro studies that included mouse macrophages and human dendritic cells, LM pectin showed an anti-inflammatory response by directly binding to TLR2–TLR1 receptors. This effect was independent of the effects due to SCFAs produced by the gut microbiota [30].

A recent study by our group at University of Nottingham showed that 4 weeks consumption of a daily supplement containing 15-20g of LM pectin significantly reduced pro-inflammatory blood markers such as TNFα (p<0.003), increased anti-inflammatory blood marker IL-10 (p=0.08), decreased TLR-2 concentration in the blood (p<0.027) and improved gut permeability with no recorded side effects in healthy volunteers [31].

- Short-Chain Fatty Acids (SCFAs) production

As mentioned above, butyrate, one of SCFAs that is produced after LM pectin fermentation in the gut, may help reduce inflammation by influencing regulatory T cells in the gut lining that Can lead to increase the level anti-inflammatory cytokines like IL-10 [14]. This might reduce the systematic inflammation.

The diagram below summarises the effects of LM pectin on gut microbiota composition and systematic inflammation pathways in individuals with MASLD:

[figure not shown]

*Study aims*

Therefore, the current research aims to study the effects of LM pectin, the dietary supplementation intervention, on pathways contributing to systematic inflammation in patients with MASLD.

# TRIAL / STUDY OBJECTIVES AND PURPOSE

## PURPOSE

This research project will explore the effects of pectin supplementation on systemic inflammation and gut microbiome composition and the consequences of these effects on general metabolic indicators, in individuals diagnosed with MASLD.

## PRIMARY OBJECTIVE

This research aims to study the effects of daily ingestion of LM pectin on inflammation pathways by measuring the blood inflammatory markers associated with physiological processes (TNFα, IL-6, IL-10, IFNᵞ, C - reactive protein, Zonulin (Haptoglobulin), IL-1β).

## SECONDARY OBJECTIVES

1. Assessment of changes in anthropometric measures.
2. Assessment of changes in general metabolic indicators, such as fasting blood glucose and other blood-based markers relevant to MASLD (e.g., CK18-M30, CK18-M65, PROC3, Enhanced Liver Fibrosis (ELF), NIS2+™, YKL-40, microRNA miR-34a-5p, liver-associated enzymes such as Alanine Aminotransferase (ALT), Aspartate Aminotransferase (AST), gamma-glutamyl transferase (GGT), Alkaline Phosphatase (ALP)), bilirubin levels, lipid profiles, and platelet counts.
3. Exploration of changes in gut microbiome composition.
4. Exploration of modifications in non-invasive physiological assessments linked to liver characteristics, such as fat content and stiffness through controlled attenuation parameter (CAP) and transient elastography.
5. Observation of alteration in fat in liver and other surrounding abdominal organs through Dixon MRI sequence in patients who will agree to have 2 MRI scans.
6. Validation of MRI measures (T2*) as a tool to measure gut permeability among MASLD patients and investigation of changes in gut permeability in participants undergoing two MRI scans.
7. Investigation the presence of gene variants such as MUC2, encoding Mucin protein, that are associated with gut permeability.
8. **DETAILS OF PRODUCT(S)**

**Description**

**Intervention Arm**

**Pectin (active substance)**

LM citrus pectin (CAS 9000-69-5) food grade pectin containing >65% galacturonic acid and ≤50 mg/kg Sulphur Dioxide

Certified as Kosher

Source: Polysaccharide found in cell walls of all plants

Appearance: White to light brown powder

Solubility: Soluble in Water (Very Slightly)

Refractive Index: 1.543

Stability: Stable under normal shipping and handling conditions

Usual Daily Dose: 5-20g

Storage: Store at room temperature

**Cocoa Powder (flavour substance)**

Nesquik®

Contains: Sugar, Fat-Reduced Cocoa Powder (23%), Emulsifier (Soya Lecithin), Salt, Vitamins (C, D), Natural Flavouring, Cinnamon.

Appearance: brown powder

Solubility: Soluble in Water

Stability: Stable under normal shipping and handling conditions

Usual Daily Dose: 4.5-9g

Storage: Store at room temperature

**Protein Powder**

Whey protein

Contains: Whey protein isolate (milk) (100%), Emulsifier (Soya Lecithin, Sunflower Lecithin)

Per 100g of whey protein: Fat 0.9g, of which saturates 0.4g, Carbohydrate 2.8g, of which sugars 1.7g, Salt 0.68g, 86g Protein

Appearance: White powder

Solubility: Soluble in Water

Stability: Stable under normal shipping and handling conditions

Usual Daily Dose: 20-30g

Storage: Store at room temperature in cool and dry place away from sunlight.

**Placebo Arm**

**Cocoa Powder (flavour substance)**

Nesquik®

Contains: Sugar, Fat-Reduced Cocoa Powder (23%), Emulsifier (Soya Lecithin), Salt, Vitamins (C, D), Natural Flavouring, Cinnamon.

Appearance: brown powder

Solubility: Soluble in Water

Stability: Stable under normal shipping and handling conditions

Usual Daily Dose: 4.5-9g

Storage: Store at room temperature

**Protein Powder**

Whey protein

Contains: Whey protein isolate (milk) (100%), Emulsifier (Soya Lecithin, Sunflower Lecithin)

Per 100g of whey protein: Fat 0.9g, of which saturates 0.4g, Carbohydrate 2.8g, of which sugars 1.7g, Salt 0.68g, 86g Protein

Appearance: White powder

Solubility: Soluble in Water

Stability: Stable under normal shipping and handling conditions

Usual Daily Dose: 20-30g

Storage: Store at room temperature in cool and dry place away from sunlight

**MRI Scans**

**Buscopan® (will be used during MRI scans as antispasmodics)**

Active ingredients: Hyoscine butylbromide 20 mg per 1 ml

Licensing authority: Medicines - MHRA/EMA

Size: 10

Unit: Ampoule

Usual Dose: 20 mg, then 20 mg after 30 minutes if required, dose may be repeated more frequently; maximum 100 mg per day

Storage: Store in a cool, dry place, away from direct heat and light

**Mannitol 2.5% / Locust bean gum 0.2% oral solution ( will be used during MRI scans as oral contrast)**

Mannitol 2.5% / Locust bean gum 0.2% oral solution

Licensing authority: None

Pack size: 1000ml

Unit: Oral Solution

**Manufacture**

**Pectin**

BOC SCIENCES INC

[name]

Shirley

New York

11967 Massachussetts

United States

**Cocoa Powder (Nesquik®)**

NESTLE UK LTD

[name]

York, England

[name]

United Kingdom

**Protein Powder**

Myprotein a THG company

BRGCS AA+ Certified

THG Nutrition Limited

[name]

Altrincham

[name]

United Kingdom

**Buscopan®**

Sanofi

[name]

Reading

Berkshire

[name]

**Mannitol**

Life Lab Supplements

[name],

Burnley

Lancashire

[name]

**Locust bean gum**

Special Ingredients Ltd

[name]

Chesterfield

[name]

**Packaging and labelling**

The study team will repackage the powders into zip lock bags labelled only as the study arm A or B based on a local SOP that was written by the study team. The repackage process will take place at a clean room at School of Medicine, University of Nottingham, E-Floor by a food hygiene trained researcher. The researcher will use electronic food scale to weigh the powders. All prepared zip bags will be kept in a dry secure location. This will be in a locked cabinet in [name] and only accessible by designated study researchers. Participants will be provided the supplements mixed with the flavour in clear plastic food safe zip lock bags. Each bag will contain either 15g of pectin with 5g of cocoa powder and 15g of whey protein powder or 30g of whey protein powder with 5g of cocoa powder.

Participants will be advised to pour 250 ml of water into a shaker bottle, then empty the whole powder inside the bag and shake the bottle until they have consistent shake. They will be advised to add water up to 50 ml if required to enhance solubility. Participants will be advised to consume one bag per day, each participant will be given 42 zip bags to be consumed within 42 days. A brochure with easy instructions will be given to each participant.

Participants will be advised to take the intervention in the morning. If they forget to take it in the morning, they will be advised to take it once they remember. Moreover, participants will be advised to avoid missing doses or overdoses as much as they can and to report missing doses or overdoses incident to the study team if that will happen. They will be given a tracker to track their daily study supplement consumption.

The study team will use pectin that is provided from BOC SCIENCES INC, United States similar to the pectin that was used on the healthy volunteer study that was previously conducted at the University of Nottingham [31].

Mannitol 2.5% / Locust bean gum 0.2% will be used as an oral contrast during u scans. It will be an oral solution that will be prepared by the MRI research team on the MRI visit day. Each drink will contain 25g of Mannitol and 2g of Locust bean gum that will be dissolved in 1000 ml of water.

Buscopan® intravenous injection will be used during MRI scans as antispasmodics. It will be prescribed, dispatched then administered by a medical doctor during MRI visit through cannula. The medical doctor will be a member of the University of Nottingham research team.

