## RANDOMIZATION AND BLINDING

The study will be a parallel design, placebo controlled, randomised intervention study in which participants will be allocated to either the intervention or placebo arm. The randomisation will be done through an online software (sealedenvelope.com) to determine intervention A or B at enrolment.

One of research team will be un-blinded and will be responsible for preparing and labelling of the intervention/placebo as either A or B based on random selection using an online software (sealedenvelope.com). A or B – pectin will be assigned to the arm in the first envelope. This information will be securely documented in a new sealed enveloped stored in the chief investigators locked desk. All other members of the team will be blinded to the assignment of A or B as the intervention.

This will be unblinded once the study is complete after the sample analysis and data analysis is complete.

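### Clear bags marked with a shared arm letter put team blinding at avoidable risk; opaque pouches with participant-specific codes would largely remove it

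*Protocol*

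**What the plan says.** Packaging and labelling (protocol, Details of product(s)) fixes the container: "Participants will be provided the supplements mixed with the flavour in clear plastic food safe zip lock bags". The bags bear nothing but the arm letter. The two fillings are "15g of pectin with 5g of cocoa powder and 15g of whey protein powder" and "30g of whey protein powder with 5g of cocoa powder".

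The product descriptions give the pectin as "Appearance: White to light brown powder", the whey as "Appearance: White powder" and the cocoa, used in both arms, as "Appearance: brown powder".

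Randomization and blinding makes one team member the unblinded preparer and then states: "All other members of the team will be blinded to the assignment of A or B as the intervention". The blind is to be lifted only when sample and data analysis are finished. The same section says that the letter given to pectin is chosen at random and kept in a sealed envelope. The synopsis (Description of interventions) and Trial/study configuration nevertheless print A as the pectin or intervention arm and B as placebo.

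Trial/study management gives the PhD researcher the study visits, the sample analysis and the data analysis. Supplements are handed over at visit 1 after randomisation (Baseline measures), and unused bags come back to the team at follow-up (Storage, dispensing and return).

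**The concern.** The protocol promises that everyone on the team but one person stays blind, and then lets the team see what is in the bags. A participant in a parallel trial meets one product. The researcher who runs visits meets both, repeatedly, and can compare them. If the two mixtures can be told apart, the shared letter turns one recognised bag into knowledge of every allocation.

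The outcomes most open to this are those that pass through human judgement:

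- symptoms reported in the weekly calls;
- advice to continue or withdraw after a reaction, which Stopping rules and discontinuation leaves to discretion;
- hand-taken weight, height and waist/hip measures, of which BMI change is a secondary endpoint;
- analysis decisions, since Statistics, Methods leaves the choice between parametric and non-parametric tests to be made on the data.

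The primary endpoint is a panel of serum biomarkers and is less exposed. It is not wholly protected, because the Full Analysis set requires a post-baseline primary assessment, so withdrawals change who contributes an assay value.

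**Working it through.** The plan gives no figure on this point to reproduce. The check is the composition of the bags, followed by a comparison of sections.

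**1. What is in each bag** (weights from Packaging and labelling)

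| Component | Pectin bag | Control bag |
|---|---|---|
| Pectin | 15 g | 0 g |
| Whey | 15 g | 30 g |
| Cocoa | 5 g | 5 g |
| Total | 15 + 15 + 5 = 35 g | 30 + 5 = 35 g |

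- Weight matches: 35 g in both arms.
- Cocoa share: 5/35 = 14.3% in both arms.
- Pectin share of the active bag: 15/35 = 42.9%.
- Whey share: 15/35 = 42.9% against 30/35 = 85.7%.

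**2. Whether the difference would show.** Pectin's listed colour runs from white to light brown, whey is white, and the same amount of brown cocoa is mixed into both. If the batch is at the white end, the mixes may look alike; if it is at the light brown end, they may not. The protocol describes no matching or check of appearance. Packing follows a local procedure that is not shown, but the clear bag is fixed in the protocol itself. A visible difference is plausible and is neither stated nor excluded.

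**3. Who sees both kinds of bag.** Baseline measures and Follow-up/end of study measures each assign one person every visit activity except blood and stool sampling and, at visit 2, the FibroScan. Trial/study management names the PhD researcher as the one who conducts visits. That researcher therefore sees bags at hand-over and may see returned ones at the visit where anthropometry is repeated. The weekly calls are made by a person whose name is removed. That this is the same researcher is likely but is an inference.

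**4. How far one recognition reaches.** Dietary intervention (6 weeks) gives 15 per arm, so 15 + 15 = 30 randomised. The synopsis total of 45 adds the 15 healthy volunteers, who receive no supplement. With two letters for 30 people, knowing what one letter means reveals all 30.

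**5. The letter itself.** The synopsis and Trial/study configuration equate A with pectin. Randomization and blinding says that the link is random and sealed. If the printed link is the one used, anyone who has read the protocol can read the allocation off the label, whatever the bag looks like.

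**The case against.** The strongest reply is that nothing in the protocol shows the two mixes to look different. A reader might infer from the product lists that the powders differ in colour. The documents do not support that: pectin's range includes white, nobody receives the bare powders, and equal cocoa in equal total weight works towards a match. This stands, and it limits the point to a risk.

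A reader might also infer that clear bags expose the allocation to participants, because pectin is listed as "Solubility: Soluble in Water (Very Slightly" and whey as soluble. That does not follow. Solubility cannot be seen in dry powder; it shows in the shaker whatever the pouch. Participants open the bag daily and see only one product. Randomization and blinding spells out masking for the team, and participant blinding is only implied by the word placebo. So the point concerns the researcher, not the participant.

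Third, the routes to bias are limited. The primary endpoint is assayed, the follow-up FibroScan is done by a research practitioner or nurse, anthropometry is taken in duplicate by standard procedures, and waist is not a listed endpoint. Bloating is not an efficacy endpoint, and the protocol says that the team will try to replace withdrawn participants. This also stands. It lowers the stakes but does not remove them for symptom reports, withdrawal decisions, BMI and analysis choices.

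Finally, one could try to size the harm through withdrawals, for example two of 15, or 13% of an arm. Nothing in the documents ties such a count to unblinding, so it is not used here.

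**Conclusion.** The point holds as an inexpensive improvement to a stated choice. Clear bags and a shared letter create an avoidable risk to the team blinding that the protocol promises. Its reach is all 30 randomised participants if one bag is recognised. The size of any bias cannot be estimated from the documents, and no claim is made that blinding has failed or will fail.

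The conclusion rests on three assumptions. The unblinded preparer is someone other than the researcher who conducts visits, which the protocol implies but does not state. The visit researcher handles or sees bags of both letters, which the visit descriptions support. The unseen local packing procedure contains no appearance matching that would remove the cue.

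The conflict over the letter needs no assumption about appearance: as written, the sections disagree on whether A is known to be pectin.

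**What to change.** In Packaging and labelling:

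- Replace the clear bags with identical opaque sealed pouches, filled by the unblinded preparer.
- Label each pouch with a code specific to the participant instead of an arm letter, so that recognising one pouch says nothing about the next. An opaque pouch alone would leave the shared letter in place.

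In Storage, dispensing and return, ask that unused pouches come back sealed.

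Reconcile the synopsis and Trial/study configuration with Randomization and blinding, so that no public text fixes which letter is pectin. The section on maintaining and breaking the code, which now relies on one envelope linking pectin to a letter, would have to hold the participant codes instead.

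The cost is modest. Each participant receives 42 bags, so 30 × 42 = 1,260 are weighed and packed in any case; the change adds a different pouch and individual labels, with each set made up against the allocation list. The limit is that the pouch does not hide texture or solubility from participants once the shake is mixed, and a remark about this in a weekly call could still hint at one person's arm. With individual codes that hint would not extend to everyone else by way of the label. Asking participants and the researcher to guess the allocation at visit 2 is optional and not part of the required change, because such guesses can also reflect perceived benefit or bloating.
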